#### 3-day food record

3-day food record is commonly used and well recognized method of dietary assessment. It requires reporting all the food and beverages consumed for three consecutive days (2-week days and 1-weekend day).

All participants of the study had to complete 3-day food record at week 0 (M0). They were previously instructed by a dietician how to fill in the food records. Patients were asked to specify the volume of consumed food with usual household measurements (e.g. cups, tablespoons) or to indicate the weight of commercial products with information recipes. After completing the food record, participants met with the dietician to review all the information for record accuracy, completeness and portion size of individual items. When needed, food models were used.

#### Food Frequency Questionnaire (FFQ)

FFQ inquires about food habits of certain time period and it is based on defined list of typical food items [26]. In comparison to other records FFQ comprises longer time of dietary intake, imposes less burden on patients and is quick and easy to complete. However the precision in quantifying intakes may be questioned. FFQ is preferred method in large cross-sectional and cohort studies in children.

For the purpose of our study FFQs were administered by registered dieticians who interviewed children and their parents in all centres. The questionnaire was modified in order to get key information about food ingredients vital for the development of obesity and metabolic syndrome e.g. saturated fatty acids, carbohydrates and antioxidants and on the other hand, these that protect organism from metabolic syndrome development, such us unsaturated fatty acids and antioxidants. Dieticians used food models for an approximate estimation of the portion consumed by the patient. The list contained over 300 products: typical dishes, raw materials, processed food, fluids and dietary supplements. Participants were asked about frequency of intake for different food during the last month in terms of day, week or month. Where available they had to provide recipes for consumed products. Parents were supporting the minors in completing the record. The FFQ was performed at the beginning (week 0) and the end of study medication treatment (week 24).

Data of consumed food were calculated to 1 day amount intake and recalculated into nutrients and energy by Energia FFQ software by [name]®. It offered a database of nutritional value of food and products as well as option to add new food items and recipes.

#### Dietetic intervention

All patients were encouraged to apply to their individually defined diet, which in combination with increased physical activity, aimed at slow reduction of body weight (approximately 0,5 kg per week) [27]. As calculated, this can be achieved with daily energy deficit of about 500 kcal. The main criterion for efficacy of our dietary intervention was the body weight loss by at least 5%.

Based on the data from dietary records (3 day food record and FFQ) dieticians instructed patients about the necessary dietary modifications and habits they had to adhere.

Patients received the following dietary recommendations:

low-calorie diet

maximum 5% of total energy from simple carbohydrates

dietary glycemic index <50

30% of the total energy from lipids with proportion of saturated/monounsaturated/polyunsaturated fatty acids as 1:1:1

adequate protein intake

The advised caloricity of the diet varied from 1500 to 1900kcal per day with respect to patient’s age, gender and level of physical activity to achieve expected weight reduction of 0,5 kg per week. Participants received examples of menus that matched necessary energy intake. Patients were aware to measure their body weight every week. In case of excessive weight gain the dietician might suggest decreased calorie intake and/or increased physical activity.

### Physical activity assessment

To assess the level of physical activity and sedentary lifestyle we used the modified International Physical Activity Questionnaire (IPAQ). This document is a open access, publically available surveillance system that was validated on large cohorts in a number of studies [28]. Answers to a set of questions assign the participant to a certain physical activity level (low, moderate or high). The IPAQ protocol is designed to be self-reported by a patient, however in our study parents assisted children in its completion.

### Outcome measures

Primary outcome measure of the study is a number of patients in whom ALT level decreased by minimum 0,3 ULN (upper limit of normal) after the 6 months of treatment with omega-3 when compared to the placebo group.

Secondary outcomes include the following parameters compared between omega-3 and placebo group after 6 months of treatment:

▪ normalization of ALT activity at week 24

▪ decrease of ALT, AST, GGTP and other liver function tests,

▪ normalization or improvement of liver steatosis on ultrasound based on Saverymuttu scoring system [29],

▪ changes in the level of fasting glucose and insulin, cholesterol and lipid profile,

▪ changes in insulin resistance markers as insulin, HOMA-IR, adipokines,

▪ alterations in the basic hematology and biochemical lab tests,

▪ difference in fat and lean body mass measurements (using electric bioimpedance TANITA® Body Composition Analyzer BC 418MA),

▪ caloric intake as well as intake of fats, fatty acids and sucrose.

Other outcomes comprise of changes in anthropometric measures of body weight (e.g. height, hip/waist circumference, triceps, subscapular and abdominal skinfolds thickness) as well as vital signs like heart rate and blood pressure.

In selected subgroups of patients we will also examine effect of treatment on:

▪ serum antioxidants e.g. glutathione, glutathione peroxidase, tromboxane,

▪ cytokines e.g. TNF-α

▪ fatty acid composition of plasma phospholipids [%wt/wt],

▪ bone mass density and fat content using dual x-ray absorptiometry (DEXA) (Lunar Prodigy, General Electric Healthcare, United States) - in a subgroup of patients who were eligible for this investigation in 2 centers,

▪ liver imaging by MR and fat content on 1H-MRS - in subgroups of patients who were eligible for these investigations,

▪ adipose tissue distribution on MRI - in a subgroup of patients who were eligible for this investigation in 1 center.

### Sample size

We decided to use decrease of ALT by 0.3 upper limit of normal value as the primary endpoint of the study. It was estimated that a sample size of 80 patients would be sufficient to reveal a difference in the treatment effect of 30% (45% in experimental group vs. 15% in control group) considering α = 0.05 and a power (β) of 80%. The number of 80 children accounted for approximately 20% withdrawals or losses. The sample size was calculated with StatDirect software version 2.7.9 (StatsDirect Ltd., England, UK).

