Recently Parker et al. published systematic review and meta-analysis of studies of omega-3 LC-PUFA (long-chain polyunsaturated fatty acids) supplementation in adults with NAFLD [20]. Nine studies (5 RCTs), involving 355 individuals were included. Patients were given either omega-3 LC-PUFA or control treatment. Duration of therapy ranged from 8 weeks to 12 months, as well as the dose of LC-PUFA - from 0,25g to 13,7g per day. In conclusion of the review, omega-3 fatty acids were claimed beneficial vs. placebo in reducing liver fat (estimated by liver biopsy, ultrasound or 1H-MRS) (effect size = ˙0.97, 95% CI: ˙0.58 to ˙1.35, p <0.001) and decreasing AST (effect size = ˙0.97, 95% CI: ˙0.13 to ˙1.82, p = 0.02) but not ALT activity. However the current data are not sufficient to set the optimal dose of LC-PUFA in NAFLD.

So far there has been only one randomized controlled trial that assessed efficacy of LC-PUFA in children with NAFLD [21]. Patients were assigned to receive 250 mg or 500 mg of DHA (docosahexaenoic acid) per day or placebo for 6 months. Beneficial results of DHA were expressed in the improvement of level triglycerides, markers of insulin resistance and liver fat assessed by ultrasound. DHA did not show significant effect on ALT activity.

Below we describe design of our multicenter, randomized, double-blind, placebo-controlled trial of omega-3 LC-PUFA supplementation in children with NAFLD.

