### Inclusion criteria

Patients had to fulfill all of the following inclusion criteria:

written consent of a patient (if at least 16 years old) and parents,

age: over 5 and below 19 years old,

overweight or obesity (BMI> 90pc according to IOTF BMI charts),

ALT activity ≥ 1,3 ULN (upper limit of normal),

hyperechogenicity of the liver on ultrasound or liver histology consistent with NAFLD/NASH (≥ 5% of hepatocytes with macrovesicular fat)

Hyper-ALT and liver steatosis on ultrasound are the most common diagnostic criteria for NAFLD used in the clinical practice. However usually the grade of ALT elevation is not defined. To increase sensitivity and specificity of diagnosis of NAFLD we used combined criteria of 1,3 ULN of ALT and liver steatosis on ultrasound. Similar diagnostic criteria were previously applied in pediatric trials on NAFLD [22,23].

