### Statistical analysis

Data will be presented as medians with quartile range. The Mann–Whitney U test will be used for comparisons of median values between groups. The calculations will be performed with PASW Statistics 18 version 18.0.0, Polar Engineering and Consulting®.

For the categorical data analysis (for the primary end point and selected secondary end points) data will be organized in contingency tables, tested for difference between observed and expected values and appropriate tests will be applied to test the null hypothesis of no difference between the groups (chi-square or Fischer’s exact test) with StatsDirect version 2.7.9 (StatsDirect Ltd., England, UK). The differences will be regarded significant at p<0.05. Statistical methods will be applied for intention-to-treat and per protocol analysis.

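### The 0.3 ULN responder cut-off makes response depend on baseline ALT, but the planned tests adjust for neither baseline ALT nor centre, and the 15% control rate has no stated basis

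*Protocol article*

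**What the plan says.** All references are to the protocol article.

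- **Endpoint (Outcome measures; Sample size).** The primary outcome is the "number of patients in whom ALT level decreased by minimum 0,3 ULN (upper limit of normal) after the 6 months of treatment". The decrease is absolute, in ULN units. The Sample size section confirms that this was a deliberate choice: "We decided to use decrease of ALT by 0.3 upper limit of normal value as the primary endpoint of the study".
- **Entry (Inclusion criteria).** "ALT activity ≥ 1,3 ULN (upper limit of normal"; no upper limit is set.
- **Planning rates (Sample size).** 80 patients are to show a "difference in the treatment effect of 30% (45% in experimental group vs. 15% in control group"). Alpha is set at 0.05 and power at 80%, and about 20% losses are allowed for. No source is given for either rate.
- **Co-intervention (Dietetic intervention).** "All patients were encouraged to apply to their individually defined diet", with increased physical activity, aiming at about 0.5 kg loss per week. This applies to both arms.
- **Prior evidence (Background).** The adult meta-analysis found no benefit on ALT. Of the single paediatric trial the article says "DHA did not show significant effect on ALT activity".
- **Analysis (Statistical analysis).** Chi-square or Fisher's exact test for categorical outcomes, including the primary one, and Mann-Whitney for continuous ones. "The differences will be regarded significant at p<0.05".
- **Randomisation.** Blocks of four, stratified by centre.
- **Status (Results).** 38 and 38 were randomised. Week-24 data collection was being finalised and the full analysis lay ahead.

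**The concern.** A fixed absolute cut-off on a measure with a wide baseline range sets a different hurdle for each child. From 1.3 ULN, response means reaching the ULN. From 3 ULN, the child responds while still at 2.7 ULN. Ordinary visit-to-visit variation in ALT, which tends to grow with the level, can therefore produce responders, more often at high baselines. Selection on a raised ALT adds regression to the mean wherever the qualifying value also serves as baseline.

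Three things follow.

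- Baseline ALT should be strongly prognostic for the primary outcome, and the planned tests leave it unused.
- A 15% control rate leaves little room for chance response plus any benefit of six months of diet and exercise.
- Cutting ALT into yes or no discards information in a trial of 76 children.

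The Discussion says that a null result would count as evidence against omega-3 in NAFLD, so avoidable imprecision in the primary comparison matters.

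**Working it through.** **1. The plan's own figure.** Inputs from Sample size: 45% v 15%, α 0.05 (taken as two-sided; the article does not say), power 80%, about 20% losses. With unpooled variance,

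n per arm = (1.960 + 0.842)² × (0.45×0.55 + 0.15×0.85) / 0.30² = 32.7, rounded up to 33.

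33 × 2 × 1.2 = 79.2, i.e. 80. (Dividing by 0.8 instead gives 41 per arm, 82 in total.) So 80 reproduces within rounding. Losses of 20% from 80 leave 64, or 32 evaluable per arm.

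**2. What 0.3 ULN means by baseline.** Relative fall = 0.3 / baseline:

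| Baseline (ULN) | Fall needed | Value reached (ULN) |
|---|---|---|
| 1.3 | 23% | 1.0 |
| 2.0 | 15% | 1.7 |
| 3.0 | 10% | 2.7 |

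Conduct of the trial gives local ULNs of 40-45 U/L, so the threshold is 12 to 13.5 U/L.

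**3. Chance response with no true change.** The article gives no within-person CV and no ALT distribution, so these are assumptions: underlying ALT lognormal (median 1.5, 2.0 or 2.5 ULN; log-SD 0.45), independent lognormal variation at both visits, entry at 1.3 ULN or above on the value that also serves as baseline, no diet effect. Simulated response:

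| Within-person CV | Response, range over the three medians |
|---|---|
| 5% | 3-7% |
| 10% | 15-21% |
| 15% | 26-30% |
| 20% | 34-35% |
| 30% | 41-44% |

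At CV 20%, response is 12-19% for observed baselines of 1.3-1.6 ULN and 51-59% for 3 ULN or more. If a separate screening value qualifies the child and a fresh value serves as baseline, the overall figure is 14-21% at CV 10% and 28-34% at CV 20%.

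**4. Cost of dichotomising.** Assume change is normal with equal SD in both arms. The shift that gives 45% v 15% is d = z(0.45) − z(0.15) = −0.126 + 1.036 = 0.911 SD. Two-sided t-test power uses noncentrality d√(n/2); responder power is exact for the uncorrected chi-square test.

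| Per arm | Noncentrality | t-test | Chi-square | Loss |
|---|---|---|---|---|
| 32 (planned evaluable) | 3.64 | 94.8% | 77.2% | 17.6 points |
| 38 (randomised) | 3.97 | 97.5% | 84.0% | 13.5 points |

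With Fisher's test, which the article also allows, responder power at 32 per arm is 68.8%.

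**5. If the control rate is above 15%.** Exact chi-square power at 32 per arm depends on what is held fixed:

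| Control rate | 30-point gap kept | 0.911 SD shift kept | Treated rate stays 45% |
|---|---|---|---|
| 15% | 77% | 77% | 77% |
| 30% | 71% | 84% | 25% |
| 40% | 71% | 83% | 8% |

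**The case against.** A reader might infer that the 15% is simply not credible. The documents do not support that. They give no ALT variability, and at a CV of about 10% or less chance response is near or below 15%. The article also condenses a fuller protocol, which may hold the source.

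A reader might also infer that one ALT value both qualifies the child and serves as baseline. The investigation schedule shows a single pre-treatment ALT column, but a selection period precedes it, and the text states neither a repeat nor its absence. Step 3 shows that chance response remains substantial either way; only the regression-to-the-mean part shrinks.

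It is tempting to say that a higher control rate underpowers the trial. That is not so in general. Power falls about 6 points if the 30-point gap holds, rises to 84% if the latent shift holds, and collapses only if the treated rate stays at 45%. Chance responders arise in both arms alike, so they do not bias the test of no difference.

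The choice of a responder endpoint is legitimate. The cut-off has a logic, since it brings the mildest eligible child to the ULN, and the sample size suits the endpoint chosen. Decrease and normalisation of ALT are already secondary outcomes. The prior null ALT findings question the assumed effect on either scale, so they are no argument against dichotomising in particular. Replacing a registered primary endpoint after recruitment has closed would invite a charge of outcome switching, and a table of power cannot change a sample already fixed at 76.

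All of this stands. What it leaves untouched is that the named tests ignore a strongly prognostic baseline and the stratification factor, both of which are already recorded.

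**Conclusion.** The concern holds as a matter of efficiency and interpretation. It does not show invalid inference.

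- **From the documents alone:** the cut-off demands a 23% fall at 1.3 ULN and a 10% fall at 3 ULN, entry has no upper limit, the named tests adjust for neither baseline ALT nor centre, and the 15% has no stated source although both arms receive a weight-loss programme.
- **On assumed variability:** the 15% is probably optimistic. Noise alone reaches it at a CV of roughly 10% and passes it above that.
- **On an assumed normal shift with equal SD:** the responder test gives up about 18 points of power at 32 evaluable per arm, or 13-14 at 38. This model differs from the lognormal one used for chance response, so the two results should not be combined.

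Type I error is not affected, and N = 80 is not an arithmetic error.

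**What to change.** Keep the registered responder endpoint primary. Before unblinding, document two analysis changes:

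1. **Primary.** Analyse response with adjustment for baseline ALT/ULN and centre, for example by logistic regression reported as a standardised risk difference with its confidence interval.
2. **First-ranked key secondary.** Replace the unadjusted Mann-Whitney test for ALT by ANCOVA of week-24 log(ALT/ULN) on arm, baseline log(ALT/ULN) and centre, reported as a ratio of geometric means.

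In the report, say where the 15% came from, or that it was a working assumption.

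**Cost.** No new data and slightly more analysis work. A ratio scale is less familiar to clinicians, but the responder rate remains beside it. One caution: at the planning rates, 32 per arm gives about 0.45×32 + 0.15×32 = 19 responders for five model terms (arm, baseline, three for the four centres). The wording should therefore name in advance what is done if the model is unstable, such as penalised likelihood or a rule for pooling small centres.

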## Results

Patients recruitment for the trial started in 2008 and ended in 2011. From a total of 86 screened participants 10 were found ineligible (11.6%). The most frequent reason for ineligibility was ALT activity <1.3x ULN. A total of 76 children with NAFLD met the inclusion criteria and were randomly assigned to receive either the omega-3 (n=38) or placebo (n=38).

The follow-up of the study is still ongoing. We are currently finalizing data collection obtained after 24 weeks of treatment. The full statistical analysis of the study results will be completed in the mid-2013.

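### Eighty patients less the stated losses of about 20% give about 76–77% power with chi-square (about 69% with Fisher's exact test), not the stated 80%

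*Protocol article*

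**What the plan says.** The Sample size section sets the target as "a difference in the treatment effect of 30% (45% in experimental group vs. 15% in control group"). The error rates behind this target are given in the words "considering α = 0.05 and a power (β) of 80" per cent. On that basis the section puts the total at 80 patients. It then states that "The number of 80 children accounted for approximately 20% withdrawals or losses", so the allowance for losses is already inside the 80. The software is named. The formula, the sidedness, any continuity correction and the number of evaluable patients are not.

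The Statistical analysis section assigns the primary endpoint to chi-square or Fisher's exact test, whichever is appropriate for the table, and says "The differences will be regarded significant at p<0.05". Intention-to-treat and per-protocol analyses are both planned.

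The Results section reports that 76 children were "randomly assigned to receive either the omega-3 (n=38) or placebo (n=38").

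**The concern.** If the 80 already includes losses of about 20%, the claim of 80% power has to hold for the 64 patients who remain. A quick check with the common two-proportion formula asks for more than 64, which suggests that losses were added in the wrong way or that the stated power applies to a larger evaluable number.

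This bears on how the result is read. The Discussion says that a finding of no effect will count as evidence against using omega-3 in NAFLD. The weight of that inference depends on the power of the trial, so the stated power should be one that the planned tests deliver.

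**Working it through.** **Inputs.** From Sample size: p₁ = 0.45, p₂ = 0.15, difference d = 0.30, α = 0.05, power 80%, total 80 including about 20% losses. From Statistical analysis: chi-square or Fisher's exact test. From Results: 38 + 38 randomised, so 1:1. Assumption: two-sided testing (z = 1.96 and 0.8416), since sidedness is not stated.

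**Step 1: reproduce the 80.** Unpooled-variance formula:

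n = (p₁q₁ + p₂q₂)(1.96 + 0.8416)² / d² = (0.2475 + 0.1275) × 7.849 / 0.09 = 32.7, so 33 per arm and 66 in total.

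66 × 1.2 = 79.2, rounded up to 80. This gives the stated figure. However, multiplying by 1.2 does not offset a 20% loss, because 80 × 0.8 = 64, not 66. Dividing gives 65.4 / 0.8 = 81.8 (82), or 66 / 0.8 = 82.5 (83).

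**Step 2: other formulas.** Pooled-variance formula, with mean proportion 0.30:

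n = [1.96√(2 × 0.3 × 0.7) + 0.8416√0.375]² / 0.09 = (1.270 + 0.515)² / 0.09 = 35.4, so 36 per arm and 72 in total. 72 / 0.8 = 90. (72 / 0.9 = 80, so this formula fits the 80 only with 10% losses.)

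Required numbers with losses handled as N / 0.8:

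| Basis | Evaluable | Randomised |
|---|---|---|
| Unpooled formula | 65.4–66 | 82–83 |
| Chi-square, exact enumeration (34 per arm, power 80.3%) | 68 | 85 |
| Pooled formula | 72 | 90 |
| Fisher, exact enumeration (41 per arm, power 80.6%) | 82 | 103 |

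**Step 3: power for 45% versus 15%.** The pooled column is the normal approximation. The chi-square (uncorrected) and Fisher columns sum the binomial probabilities of all tables that the test declares significant.

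| Situation | Per arm | Pooled formula | Chi-square | Fisher |
|---|---|---|---|---|
| 80 planned, no losses | 40 | 84.7% | 85.2% | 79.3% |
| 80 planned, 66 evaluable (17.5% lost) | 33 | 77.0% | 78.8% | 68.6% |
| 80 planned, 20% lost | 32 | 75.7% | 77.2% | 68.8% |
| 76 randomised, no losses | 38 | 82.8% | 84.0% | 77.6% |
| 76 randomised, 20% lost (60.8, about 30 per arm) | 30 | 72.9% | 73.7% | 64.5% |

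**Step 4: detectable difference.** At 30 per arm with 15% in the control group, 80% power needs about 48% responders with chi-square (33 points) and about 51–52% with Fisher (36–37 points).

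**Step 5: which test is likely.** At 32 per arm and a pooled rate of 30%, the expected counts are 32 × 0.30 = 9.6 and 32 × 0.70 = 22.4. Both are well above the usual threshold of 5, so chi-square would normally be chosen.

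**The case against.** The best defence is that the 80 can be reproduced. The article fixes no formula, the unpooled version is standard, and by its own approximation power at 64 evaluable is 79.1%. The loss allowance is only approximate, and 66 evaluable of 80 is a loss of 17.5%. This stands as an account of where the figure came from, and it shows that the slip is small. It does not make the stated power true for the named tests: at 33 per arm chi-square still has 78.8% and Fisher 68.6%.

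A second defence is that expected counts point to chi-square, so the Fisher figures should not set the size of the problem. That also stands. The main shortfall is about 3 to 4 points.

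Three stronger readings are tempting, and the documents do not support them:

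- A reader might infer that the plan's inputs require 90 patients, or over 100. Those totals depend on a choice of formula or test that the article leaves open, and the smallest two-sided answer is 82.
- A reader might take the 76 randomised as part of the miscalculation. It is an openly reported recruitment result, 4 short of 80 (5%). If all 76 are analysed without loss, chi-square power is 83–84%.
- A reader might put the risk of missing the planned effect at 25–35%. That does not describe the planned design, where it is 23–24% with chi-square and 31% with Fisher. Figures near 26–35% arise only for 76 randomised with 20% lost, and the article gives no attrition figure.

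A one-sided calculation (56 evaluable, 70 randomised) would fit within 80, but the article nowhere states a one-sided test.

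**Conclusion.** The sample-size statement is wrong as written, by a modest amount. At the 64 evaluable patients that it implies, power for 45% versus 15% is about 76–77% with chi-square and about 69% with Fisher's exact test, against the stated 80%. Fisher's test falls just short (79.3%) even if none of the 80 is lost. The conclusion rests on two-sided testing at 0.05, equal arms, and losses that leave the analysis. How losses enter the intention-to-treat analysis is not described, so that last assumption is one scenario among several. Separately, the text labels power as β; β is the type II error rate and power is 1 − β. No test, estimate or decision rule is affected. What changes is the power against which a null result will be read.

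**What to change.** Enrol no more patients. Rewrite the Sample size paragraph to:

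- state the formula, the sidedness, the test assumed and the number of evaluable patients behind the calculation, with losses handled by dividing by 0.8;
- describe the 76 randomised as a recruitment result, and report power for 45% versus 15% as a range: about 83–84% (chi-square) and 78% (Fisher) with no losses, and about 73–74% and 65% if 20% are lost;
- give the detectable difference at 80% power, about 33 points from 15% with chi-square and 36–37 points with Fisher at 30 per arm;
- relabel power as 1 − β.

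The cost is one paragraph. The stated power becomes somewhat less favourable, and the 24-week analysis, still to come when the article was written, can be read against it.
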